### Data preprocessing and statistical analysis

2.6

EEG data will be preprocessed using EEGLAB (v2024.0) in MATLAB R2024b following a predefined pipeline. Continuous data will be band-pass filtered between 0.1 and 40 Hz and segmented into epochs time-locked to rectal distension onset (−200 to 800 ms). Independent component analysis (ICA) will be applied to identify and remove components associated with ocular, muscular, and cardiac artifacts, based on spatial topography, power spectra, and time-course characteristics.

Event-related potentials (ERPs) will be quantified at predefined fronto-central electrodes. ERP components of interest (N1, P2, and P3) will be defined within fixed latency windows based on prior interoceptive ERP literature (N1: 80–150 ms; P2: 150–250 ms; P3: 250–400 ms). Mean amplitude and peak latency within these windows will be extracted for statistical analysis.

Time–frequency analyses will be conducted using event-related spectral perturbation (ERSP) methods, with baseline normalization relative to the −200 to 0 ms pre-stimulus interval. Power changes in the theta (4–7 Hz) and alpha (8–12 Hz) bands will be quantified.

Group-level comparisons among UWS, MCS, and healthy control participants will be performed using one-way ANOVA for each predefined electrophysiological outcome. *Post hoc* pairwise comparisons will be corrected for multiple testing using the Tukey HSD procedure. Effect sizes (η^2^ or Cohen’s d, as appropriate) will be reported to inform the design of future confirmatory studies. All analyses will be restricted to predefined electrodes, frequency bands, and latency windows to limit multiple comparisons and reduce the risk of false-positive findings.

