#### Rectal stimulation paradigm

2.4.2

Gut-related interoceptive stimulation will be delivered using a controlled rectal balloon distension paradigm. A lubricated balloon-tipped catheter (liquid paraffin) will be inserted such that the distal balloon is positioned approximately 10 cm from the anal verge, guided by catheter scale markings. Participants will be maintained in a left lateral decubitus position throughout the procedure.

Stimulation will be administered using a computer-controlled inflation–deflation device developed with participation from the research team, ensuring precise temporal and volumetric control. Each trial will consist of rapid balloon inflation to a fixed volume of 60 mL, reaching target volume within 150 ms, followed by passive deflation.

The inter-stimulus interval (ISI) will be pseudo-randomized at 12 ± 4 s to minimize anticipatory responses and neural habituation. A total of 35 stimulation trials will be delivered per participant, resulting in an approximate stimulation duration of 7–9 min.

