### Aims and outcome measures

2.7

The primary aim of this study is to assess the feasibility of recording gut-related interoceptive EEG responses in patients with disorders of consciousness under standardized stimulation conditions.

The primary outcomes are predefined electrophysiological measures, including:(1) ERP component amplitude and latency (N1, P2, P3) time-locked to rectal distension, and.(2) Event-related spectral perturbation (ERSP) in the theta (4–7 Hz) and alpha (8–12 Hz) frequency bands.

Secondary exploratory outcomes include group-level comparisons of these electrophysiological measures among UWS, MCS, and healthy control participants, as well as exploratory associations between EEG markers and CRS-R total scores and subscale scores.

All outcomes are exploratory and group-level in nature. This study is not designed to support individual-level diagnostic classification or clinical decision-making, but rather to assess feasibility and to provide preliminary effect size estimates that may inform the design of future hypothesis-driven and validation studies.

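### Peak latency, a primary outcome, is scored in fixed windows with no requirement that a component be present, so group differences in response rate can appear as latency or variance differences

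*Protocol article*

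**What the plan says.** The protocol article, section 2.6 (Data preprocessing and statistical analysis), sets the windows as "N1: 80–150 ms; P2: 150–250 ms; P3: 250–400 ms" and continues: "Mean amplitude and peak latency within these windows will be extracted for statistical analysis". Comparisons among UWS, MCS and healthy controls "will be performed using one-way ANOVA for each predefined electrophysiological outcome", followed by Tukey's procedure. The only stated restriction is this: "All analyses will be restricted to predefined electrodes, frequency bands, and latency windows". Presence of a response is not on that list, and the article gives no signal-to-noise threshold and no coding for an absent component.

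Section 2.7 (Aims and outcome measures) names as primary "ERP component amplitude and latency (N1, P2, P3) time-locked to rectal distension". The primary aim in the same section is to "assess the feasibility of recording gut-related interoceptive EEG responses in patients with disorders of consciousness". Between-group comparisons and associations with CRS-R scores are secondary and exploratory. Section 2.6 adds that effect sizes "will be reported to inform the design of future confirmatory studies".

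**The concern.** The two measures taken from each window behave differently when there is no response. Mean amplitude falls towards zero, which is informative. Peak latency does not go missing. The search returns the time of the largest noise deflection in the window, and the ANOVA treats that number like a real latency.

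This matters here because the existence of a response in these patients is what the study sets out to learn. If the share of recordings with a response differs between groups, the groups' latency distributions contain different proportions of noise. A reader could take the resulting difference for slower or faster processing when it reflects how many participants responded and where the window was placed. The latency effect sizes, and any correlation of latency with CRS-R, would carry the same mixture into the design of later studies.

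**Working it through.** The article gives no figure for latency to reproduce. Its sample size rests on pilot amplitude and does not bear on this point.

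**Inputs from the article.** Windows 80–150, 150–250 and 250–400 ms (section 2.6); 15 participants per group (sections 2.2 and 2.5); one-way ANOVA (section 2.6).

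**Step 1: what the rule returns from noise alone.** For a peak uniform in a window of width w, the mean is the midpoint M and the SD is w/√12. Simulated noise averages (1/f-type power, 0.1–40 Hz, baseline −200 to 0 ms; the noise model is an assumption) give:

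| Component | Midpoint (ms) | w/√12 (ms) | Simulated mean (SD) (ms) | Peak on window edge |
|---|---|---|---|---|
| N1 | 115 | 70/√12 = 20 | 115 (24) | 20% |
| P2 | 200 | 100/√12 = 29 | 200 (33) | 15% |
| P3 | 325 | 150/√12 = 43 | 325 (48) | 10% |

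**Step 2: mixing responders and non-responders.** Let a share p of one group have no response, and let responders in both groups have the same true latency μ with SD σ. Then

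- mean shift = p(M − μ)
- variance = p·w²/12 + (1 − p)σ² + p(1 − p)(M − μ)²

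For P3, with p = 0.5, σ = 15 ms and μ = 280 ms, the shift is 0.5 × (325 − 280) = +22.5 ms. The variance is 0.5 × 1875 + 0.5 × 225 + 0.25 × 2025 = 1556, so the SD is 39 ms against 15 ms in controls.

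**Step 3: how often a t-test declares a difference.** 15 against 15, no absent responses in controls, noise peaks uniform in the window, two-sided 5% level, 40,000 runs per row. The values of μ, σ and p are assumptions.

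| True P3 latency (ms) | Shift at p = 0.5 (ms) | SD (ms) | Declared different |
|---|---|---|---|
| 280 | +22.5 | 39 | 50% |
| 290 | +17.5 | 37 | 34% |
| 300 | +12.5 | 35 | 20% |
| 310 | +7.5 | 33 | 11% |
| 325 | 0 | 32 | 5% |
| 340 | −7.5 | 33 | 11% |
| 370 | −22.5 | 39 | 50% |

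The share without a response matters as much. At 300 ms the rate is 8% for p = 0.25, 20% for p = 0.5 and 52% for p = 1. With p = 0 it is 5% at every latency.

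**Step 4: the planned three-group ANOVA.** Simulated waveforms, 15 per group, component peak 4 times the noise SD, between-subject latency SD 10 ms, same true latency in all responders (all assumed). True latencies off the midpoint were 95 and 135 ms (N1), 170 and 230 ms (P2), 280 and 370 ms (P3).

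| Share absent in the three groups | N1 | P2 | P3 |
|---|---|---|---|
| 0 / 30 / 60% | 31–33% | 38–40% | 40–43% |
| 0 / 50 / 100% | 68% | 77–78% | 82–83% |

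With everyone responding, rejection was 4.5–5.3%. With the true latency at the midpoint it stayed at 5–6.5% even with absent responses, but the P3 SD rose from 14 to 48 ms across groups, about 3.5-fold. That breaks the equal-variance assumption of ANOVA and Tukey and distorts Cohen's d.

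**The case against.** The strongest objection is that this is partly silence. The article does not say that latency is scored in every participant, and a rule for absent peaks could sit in a full protocol or analysis plan that is not shown. That limits the point but does not remove it. The extraction and comparison rule is stated, its restrictions are listed, and applied as written it scores noise as latency.

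The objection to the size is sound. The article gives no latency, latency SD, signal-to-noise figure or share of absent responses, and the result moves from 50% to 5% on the assumed latency alone.

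A reader might infer that UWS patients are the group expected to lack a component. The documents do not say so. The article states no directional hypothesis, and its introduction notes that some UWS patients have covert awareness. A reader might also infer from "A total of 35 stimulation trials will be delivered per participant" that noise peaks will be common, but nothing in the article quantifies the signal-to-noise ratio at that number.

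Two further points soften the consequence. Mean amplitude is reported beside latency, so an absent response would be visible there. And the comparisons are labelled exploratory, with no individual classification to follow. Both are true, but latency is still a primary outcome with its own test and effect size.

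**Conclusion.** The concern holds as a defect in the stated rule: peak latency is extracted and compared with no condition that a component be present, in a study whose primary aim leaves that presence open. The location and wide spread of a noise latency follow closely from the article's windows. The rejection rates do not. They rest on assumed latencies, spreads and response shares, and they range from the nominal 5% to about 50% in the two-group P3 illustration with half of one group not responding.

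It would go too far to read this as a predicted delay in patients. The shift needs unequal response rates and a true latency off the window midpoint, and it reverses sign on the other side of the midpoint. Nor is it a difference arising from nothing: in these scenarios the groups do differ, in how many respond. The error is to attribute that difference to timing. The plan should be changed, but the point does not undermine the amplitude outcomes.

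**What to change.** Add to section 2.6 or the analysis plan:

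- A predefined criterion for each component being present, for example mean amplitude in the window outside the 95% range of surrogate epochs from the same recording. Such a criterion will still pass some recordings without a response by chance, and this should be acknowledged.
- The number and percentage with a response, by group and component. This also serves the feasibility aim directly.
- Peak latency analysed only in those with a response, and labelled as conditional on a response. The same applies to latency in the CRS-R associations.
- Mean amplitude kept for every participant.

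Replacing the peak by a fractional-area latency is not needed and has its own drawback. In a fixed window it is also pulled to the midpoint: for a Gaussian component of SD 60 ms in the P3 window, a true 280 ms reads 302 ms and a true 370 ms reads 348 ms.

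The cost is wording and a little scripting, with no new data. The downside is fewer participants, and a selected subset, in the latency analysis, so group comparisons of latency will be less precise and should be read descriptively.

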#### EEG acquisition parameters

2.4.3

Continuous EEG will be recorded using a 32-channel system (iRecorder W32, Niantong Intelligent Technology, Shanghai, China). Electrodes will be positioned according to the international 10–20 system, with particular emphasis on fronto-central and parietal regions associated with interoceptive and cognitive processing.

A wet electrode cap based on Ag/AgCl cup electrodes will be used. Conductive gel will be applied to each electrode site to reduce scalp impedance, which will be maintained below 5 kΩ throughout the recording. EEG signals will be sampled at 1000 Hz, with an online bandwidth of 0.1–100 Hz. Signals will be referenced to the bilateral mastoids, with the ground electrode placed at a standard frontal location.

Strict data quality control procedures will be implemented throughout acquisition, including continuous impedance monitoring and artifact inspection.

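### The −200 to 0 ms ERSP baseline is too short for low theta at any cycle count, and for both bands at three cycles

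*Protocol article*

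**What the plan says.** Section 2.6 of the protocol article describes one segmentation: continuous data are "segmented into epochs time-locked to rectal distension onset (−200 to 800 ms". For the spectral analysis it names the method, "event-related spectral perturbation (ERSP) methods", and fixes the reference: "with baseline normalization relative to the −200 to 0 ms pre-stimulus interval". It continues: "Power changes in the theta (4–7 Hz) and alpha (8–12 Hz) bands will be quantified". It gives no separate epoch for this analysis, no window length and no number of cycles.

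Section 2.7 lists as the second of two primary outcomes "Event-related spectral perturbation (ERSP) in the theta (4–7 Hz) and alpha (8–12 Hz) frequency bands".

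Two other settings bear on the remedy. Section 2.4.3 has the EEG recorded continuously at 1000 Hz. Section 2.4.2 states: "The inter-stimulus interval (ISI) will be pseudo-randomized at 12 ± 4 s".

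**The concern.** An ERSP value is post-stimulus power relative to pre-stimulus power, so it is only as good as the pre-stimulus estimate. Power at a given frequency is estimated over a window of one or more cycles, and at low frequencies that window is long. Here all the pre-stimulus data in the stated epoch amount to 200 ms, and the baseline runs right up to stimulus onset. If the windows do not fit before onset, there are two possibilities: no baseline estimate exists, or the baseline contains part of the response it is meant to be compared with.

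At stake are a primary outcome and the effect sizes that the study intends to pass on to later confirmatory work.

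**Working it through.** **Inputs.** Baseline −200 to 0 ms, epoch −200 to 800 ms, bands 4–7 and 8–12 Hz (all Section 2.6). The number of cycles c is not in the document; c = 1, 2 and 3 are shown as an assumption. The plan has no figure of its own to reproduce.

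**Step 1: does one whole window fit in the baseline?** Window length W = c × 1000/f ms. It fits if W ≤ 200 ms, that is, f ≥ c/0.2 s: 5 Hz for c = 1, 10 Hz for c = 2, 15 Hz for c = 3.

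| f (Hz) | Cycles in 200 ms | W at c = 1 / 2 / 3 (ms) | Fits for |
|---|---|---|---|
| 4 | 0.8 | 250 / 500 / 750 | none |
| 5 | 1.0 | 200 / 400 / 600 | c = 1 |
| 7 | 1.4 | 143 / 286 / 429 | c = 1 |
| 8 | 1.6 | 125 / 250 / 375 | c = 1 |
| 10 | 2.0 | 100 / 200 / 300 | c = 1, 2 |
| 12 | 2.4 | 83 / 167 / 250 | c = 1, 2 |

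This test is lenient, since it asks for only one clean window. Frequencies below 5 Hz fail it at every cycle count.

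**Step 2: ERSP computed on the stated epoch.** Windows that stay inside the epoch have centres from −200 + W/2 to 800 − W/2. With c = 3:
- 4 Hz: −200 + 375 = +175 ms to 800 − 375 = +425 ms.
- 7 Hz: +14 to +586 ms.
- 8 Hz: −12.5 to +612.5 ms. The earliest window reaches +175 ms, so 175/375 = 47% of it lies after onset.
- 12 Hz: −75 to +675 ms. The earliest window reaches +50 ms, so 50/250 = 20% of it lies after onset.

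Theta therefore has no baseline estimate at all, and every alpha estimate in the baseline crosses onset. With c = 1 at 4 Hz the first valid centre is −75 ms, and its window reaches +50 ms.

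**Step 3: ERSP computed on a longer segment, baseline kept at −200 to 0 ms.** A window centred at t reaches t + W/2. At 4 Hz with c = 3, even the centre at −200 ms reaches +175 ms, so every baseline estimate contains post-stimulus data. At 8 Hz only 12.5 of the 200 ms of centres are clean; at 12 Hz, 75 of 200 ms.

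An illustrative simulation shows the size (white noise, power multiplied by 4 from 0 to 400 ms, true change 6.0 dB, three-cycle Hann-tapered wavelet, 6,000 trials):

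| f (Hz) | Baseline inflated by | ERSP, −200 to 0 ms baseline | ERSP, clean baseline |
|---|---|---|---|
| 4 | 1.64 | 3.48 dB | 5.63 dB |
| 7 | 1.34 | 4.71 dB | 5.98 dB |
| 8 | 1.32 | 4.70 dB | 5.92 dB |
| 12 | 1.23 | 5.12 dB | 6.04 dB |

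**Step 4: dependence on the size of the response.** In this model the baseline is inflated by 1 + λ(R − 1), where R is the true power ratio and λ the leaked share. At 4 Hz, λ = 0.64/3 = 0.213. For R = 4 the loss is 10·log10(1.64) = 2.15 dB. For R = 2 it is 10·log10(1.213) = 0.84 dB. The larger response loses more, so differences between groups are compressed.

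**The case against.** Several stronger readings are tempting, and the document does not support them.

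- A reader might infer that the 1,000 ms epoch is too short for theta altogether. It is not: with three cycles at 4 Hz it still allows post-stimulus centres from +175 to +425 ms. The fault is the short pre-stimulus part and a baseline that ends at onset.
- A reader might infer that the whole ERSP outcome lacks a clean baseline whatever the settings. With one cycle, 5–7 Hz and all of alpha fit, though with very poor frequency resolution; with two cycles, 10–12 Hz fits. Only frequencies below 5 Hz fail throughout.
- A reader might say that the analysis can resolve only 5 Hz (1/0.2 s). That holds for a 200 ms window, not for a 750 ms one.
- A reader might combine the missing baseline points with the leakage. They are alternatives that depend on the segment analysed.
- A reader might expect healthy controls to lose most. The document does not say which group responds most.

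It is also fair to say that a condensed article may leave cycles, padding and a separate ERSP segment to a fuller document. That answers Step 2 but not Step 3, because the baseline is a stated setting and a longer segment does not move it away from onset. The simulation places the power rise exactly at onset; a later rise would leak less, so its decibel figures are illustrative only.

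Finally, the study is exploratory, its aim is feasibility, the group comparisons are secondary, and the sample size rests on ERP amplitude. This limits the consequences. It does not remove them, because ERSP is a primary outcome and effect sizes are an intended product.

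**Conclusion.** The concern holds in limited form. The stated baseline is too short for the lower part of theta at any cycle count, by arithmetic that needs no assumption (250 ms against 200 ms). How far the problem extends depends on the unstated cycle count: all of theta and alpha below 10 Hz with two cycles, and both bands with three.

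With three cycles on the stated epoch, theta has no valid baseline estimate. On a longer segment with the same baseline, the measured change shrinks toward zero, by about 2.2 dB at 4 Hz and 1.2 dB at 8 Hz under the simulation's assumptions, and by more where the response is larger. ERP amplitude and latency are not affected. Because the fault lies in a stated setting for a primary outcome, it should be corrected before the data are analysed.

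**What to change.** Keep −200 to 800 ms for the ERPs. For ERSP:

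1. Cut separate epochs of about −2,000 to +3,000 ms from the continuous recording. If 12 ± 4 s is a range, the shortest interval is 8 s; the next epoch then starts at 8 − 2 = 6 s, after the previous one ends at 3 s. If ± 4 s is not a hard range, check the shortest interval actually delivered.
2. Place the baseline centres so that they end at least half a 4 Hz window before onset. With three cycles (half-window 375 ms), centres from −1,000 to −400 ms use data from −1,000 − 375 = −1,375 ms to −400 + 375 = −25 ms, all before the stimulus.
3. State the number of cycles and the post-stimulus ERSP window.

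The cost is a change of analysis wording and a second segmentation of data already being recorded. No new data are needed and the ERP analysis is unchanged. Artefact handling must cover the longer epochs, which may cost a few of the 35 trials.

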### Sample size estimation

2.5

An *a priori* power analysis was conducted using G*Power (v3.1.9.7) based on pilot ERP amplitude data (*n* = 4 per group). Using an independent-samples t-test model, the pilot data yielded a Cohen’s d of 1.13. With a two-tailed *α* = 0.05 and 80% power, the minimum required sample size was estimated at 13 participants per group. To account for potential data loss or dropout, the target sample size was increased to 15 participants per group.

Given the exploratory nature of this study, the sample size is intended to support feasibility assessment and preliminary effect size estimation rather than definitive diagnostic accuracy evaluation. The pilot-based power calculation was performed using a pairwise comparison framework to estimate effect size magnitude; group-level comparisons in the present study are intended for descriptive and exploratory purposes rather than confirmatory hypothesis testing.

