From a public health perspective, the potential relevance of this work extends beyond individual-level assessment. Advanced neuroimaging techniques such as fMRI and FDG-PET, while informative, are costly, resource-intensive, and often inaccessible in low and middle-income settings. EEG-based paradigms that can be implemented at the bedside offer a more scalable and equitable approach to DoC research. If feasibility and systematically characterizable neural responses are demonstrated, this line of research may contribute to the development of accessible assessment strategies aligned with public health priorities of feasibility, equity, and responsible resource utilization.

Several limitations of the present protocol should be acknowledged. The relatively small sample size and single-center design limit generalizability and preclude conclusions regarding diagnostic performance or individual-level classification. Moreover, interoceptive processing may be influenced by factors such as medication exposure, autonomic dysfunction, and gastrointestinal comorbidities, which will require systematic control in future studies. In addition, this protocol is not designed to establish causal relationships between interoceptive neural responses and conscious awareness. These considerations underscore the exploratory nature of the present work and highlight the need for subsequent multicenter and longitudinal investigations with larger cohorts and predefined validation frameworks.

Importantly, this protocol is intended to serve as an initial methodological step within a staged translational research pathway rather than as a diagnostic validation study. The primary objective is to establish feasibility, tolerability, and signal-level characteristics of gut-related interoceptive EEG responses under standardized bedside conditions, thereby generating essential methodological parameters and effect size estimates to guide subsequent multicenter and hypothesis-driven investigations.

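### η² is biased upward with three groups of 15, so it is a poor planning figure for later studies; the shortfall runs from about 15–18% at the pilot effect to about half if the true η² is near 0.05

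*Protocol article*

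**What the plan says.** Section 2.6 (Data preprocessing and statistical analysis) plans a one-way ANOVA across UWS, MCS and healthy controls for each electrophysiological outcome, with Tukey pairwise comparisons. It names η² or Cohen's d as the effect size measures and gives their use: they "will be reported to inform the design of future confirmatory studies".

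That use recurs. Section 2.7 says the study is meant, besides assessing feasibility, "to provide preliminary effect size estimates that may inform the design of future hypothesis-driven and validation studies". Section 2.5 gives preliminary effect size estimation as one purpose of the sample size. The Discussion lists among the expected results "effect size estimates to guide subsequent multicenter and hypothesis-driven investigations". The formal primary aim in section 2.7 is feasibility.

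The only effect size stated is in section 2.5: "the pilot data yielded a Cohen’s d of 1.13", "based on pilot ERP amplitude data (*n* = 4 per group". From it "the minimum required sample size was estimated at 13 participants per group", and "the target sample size was increased to 15 participants per group". No true η² or Cohen's f is given anywhere.

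**The concern.** The sample η² is the between-group share of the total sum of squares. Chance differences between group means add to the between-group sum, so η² is positive even when the groups do not differ, and too large on average when they do. In large samples this is negligible. With 45 participants in three groups it is not, because the excess is of the same order as a small-to-medium effect.

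The protocol intends these figures for designing the next study. Required sample size varies roughly with the inverse of η²/(1 − η²), so an inflated value gives a study that is too small. The size of the damage depends on the true effect, which has to be assumed.

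**Working it through.** **Inputs from the documents.** k = 3 groups, 15 per group, N = 45, ANOVA degrees of freedom 2 and 42 (sections 2.2, 2.5, 2.6). Pilot d = 1.13 from 4 per group (section 2.5). For the later study I keep the plan's own settings: "With a two-tailed *α* = 0.05 and 80% power" (for the ANOVA, the F test at 0.05).

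**The plan's own figure.** n per group = 2(1.96 + 0.842)²/1.13² = 12.3, rounded up to 13, which reproduces the stated minimum. The exact noncentral t gives 78.9% power at 13, 82.1% at 14 and 84.8% at 15. The difference of one is covered by the target of 15 if no more than one participant per group is lost.

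**Bias with no effect.** E(η²) = (k − 1)/(N − 1) = 2/44 = 0.045.

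**Translating the pilot d to η².** Assume 1.13 is the largest of the three pairwise differences.
- Third group midway: f = d/√6 = 0.461, η² = f²/(1 + f²) = 0.175.
- Third group equal to one of the others: f = d√2/3 = 0.533, η² = 0.221.

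**Bias with an effect.** The between-group sum of squares was drawn as noncentral chi-square on 2 df with λ = 45f², and the within-group sum as chi-square on 42 df. n per group for 80% power comes from the noncentral F, first at the true η² and then at the mean sample η². The last column is the real power of a study sized on the mean sample η². All true values are assumptions.

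| True η² | Mean η² | Mean ω² | n needed | n planned | Ratio | Real power |
|---|---|---|---|---|---|---|
| 0.02 | 0.064 | 0.019 | 159 | 48 | 0.30 | 31% |
| 0.04 | 0.083 | 0.038 | 79 | 37 | 0.47 | 46% |
| 0.05 | 0.092 | 0.048 | 63 | 33 | 0.52 | 51% |
| 0.059 (f = 0.25) | 0.101 | 0.057 | 53 | 30 | 0.57 | 54% |
| 0.10 | 0.139 | 0.097 | 30 | 21 | 0.70 | 63% |
| 0.138 (f = 0.40) | 0.175 | 0.134 | 22 | 17 | 0.77 | 70% |
| 0.175 (pilot, lower) | 0.211 | 0.170 | 17 | 14 | 0.82 | 73% |
| 0.221 (pilot, upper) | 0.254 | 0.215 | 13 | 11 | 0.85 | 74% |

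Mean ω² stays close to the truth throughout, and so does ε² (0.058 at a true 0.059).

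**One study as it would be read.** For an observed η² of 0.10, F = (0.10/2)/(0.90/42) = 2.33. Then ω² = 2(F − 1)/[2(F − 1) + 45] = 2.67/47.67 = 0.056, and ε² = 1 − 0.90 × 44/42 = 0.057. The n per group is 30 from η², 56 from ω² and 55 from ε². The 95% interval for the effect runs from 0 to about 0.26.

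**Cohen's d.** At 15 per group (28 df) the small-sample factor is J = 0.973, so d is inflated by 1/0.973 − 1, about 3%. Sample size scales with J² = 0.947, so n would be about 5% too small. At the pilot's 4 per group (6 df), J = 0.869 and the corrected value is 1.13 × 0.869 = 0.98.

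**The case against.** **The size depends on an assumption the protocol does not make.** A reader might infer that any study sized on this η² would be half the size needed. The documents do not support that. The half-size result needs a true η² of about 0.04 to 0.06; at the only effect the protocol gives, the shortfall is about 15 to 18%. This objection stands. The pilot effect is not a safe anchor either: with 4 per group, the 95% interval for d runs from about −0.43 to 2.61, so small effects are compatible with it.

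**Effect sizes are not the main product.** A reader might also infer that they are. The primary aim is feasibility, the group comparisons are secondary and exploratory, and the estimates are called preliminary. This stands too: they are one stated purpose beside feasibility.

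**Cohen's d is named as well, and the plan's own sizing used it.** At 15 per group its bias is minor. Treating it as the same problem as the pilot d would equate a 3% inflation with one of about 15% (1/0.869). The case rests on η².

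**Later planners can convert.** ω² and ε² follow exactly from η² and the degrees of freedom, and nothing in the protocol says a later trial must use the raw figure. That is true and limits the harm, but it relies on every later user making a correction that the protocol could make itself.

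**This is analysis-plan detail.** That holds for intervals: their absence from an article is not a fault. It does not hold for the estimator, which section 2.6 names together with its use.

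**Imprecision is the larger problem.** At a true η² of 0.059 the standard deviation of η² (0.074) exceeds its bias (0.042), and that of ω² is similar (0.076). This stands, and is why the intervals belong in the remedy.

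**Conclusion.** The concern holds in a bounded form. Section 2.6 names η² for a planning use to which it is poorly suited with 15 per group. It is about 0.035 to 0.045 too high for true values from zero to about 0.175, whereas ω² and ε² are nearly unbiased.

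The consequence must be stated as a range. A later study sized on the average η² would be about 15 to 18% too small at the pilot effect, about half the needed size for a true η² of 0.04 to 0.06, and a smaller fraction below that. These figures assume normal data with equal variances, all 45 participants analysed, 80% power at 0.05, a later study of the same three-group design, and 1.13 as the largest pairwise difference. A single study's η² will scatter widely around the averages used here.

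Nothing in the present study's tests or conduct is affected. The change is worth making because it concerns a stated output and costs almost nothing.

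**What to change.** In section 2.6, replace η² with ω² (or ε²) for the ANOVA and Cohen's d with Hedges' g for the pairwise contrasts, each with a 95% confidence interval. Add that the point estimates are imprecise at this sample size and should not be used alone to size later studies. η² may be kept alongside for comparison with other literature.

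The cost is one or two sentences, with no extra data or participants and no change of test. Reported effects will look smaller. ω² will be zero or negative in a sizeable share of studies when the true effect is small (about 27% at a true η² of 0.059) and should be reported as it falls. The change corrects bias and leaves imprecision as it is; the intervals only make that visible.

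I would not add a rule that later studies be sized on the lower limit of an interval. At a true η² of 0.059 that limit is zero in about 44% of studies for a 60% interval and about 59% for an 80% interval, which gives no finite sample size. Nor can this protocol bind later trials.
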